### Sampling and recruitment of study participants

Figure 3 summarises the sampling and recruitment of study participants for the baseline survey. First, we sampled intervention districts and selected geographically and administratively matched comparison districts. Then, we randomly sampled intervention villages in two steps, first sampling the blocks and then the villages. Finally, we pair-matched intervention villages with villages from the comparison districts and selected the best matched 426 pairs as discussed next.

**Figure 3 F3:**
[figure not shown]
Sampling of study participants from Madhya Pradesh and Bihar. AWC, Anganwadi Centre; AWW, Anganwadi worker; CAS, Common Application Software; ICDS, Integrated Child Development Services; ISSNIP, ICDS Systems Strengthening and Nutrition Improvement Programme. Sources: # Women and Child Development Department, Government of Madhya Pradesh (MIS) http://mpwcdmis.gov.in/ (See1m5bxnuzmixun00bsctvfj))/DataEntryAwc.aspx (Accessed 8 June 2018); & Integrated Child Development Services, Government of Bihar http://www.icdsbih.gov.in/AnganwadiCenters.aspx?GL=16 (Accessed 8 June 2018); *Programme documentation from implementing agencies.

*Sampling of Intervention and Comparison Districts*: We randomly sampled three pairs of geographically and administratively matched intervention and comparison districts which shared a boundary and belonged to the same ICDS division to control for division-level confounders related to ICDS administration and management as well as cultural, social, environmental and economic factors at the micro-region scale. Within each state, we first sample three intervention districts. The corresponding control districts were selected by default if only one eligible district was available within the division, or randomly, if multiple comparison districts were available. In MP, the sample purposively included one pair of *tribal-only* districts from an equity-focused evaluation perspective. Figure 4 depicts the states and districts included in the evaluation.

**Figure 4 F4:**
[figure not shown]
Sampled intervention and comparison districts. Green areas indicate intervention districts. Blue areas indicate comparison districts.

*Selecting Matched Pairs of Treatment and Control Villages*: From each selected district, we randomly sampled two blocks in MP and three blocks in Bihar. Next, we randomly sampled 345 villages from six intervention blocks in MP and 315 villages from nine ICDS-CAS blocks in Bihar. In both states, the sample frame was restricted to villages with a population of 500 or more to increase the possibility that the villages are sufficiently large to be served by dedicated AWCs. Next, we matched the sampled treatment villages with villages from the paired comparison district using a 1:1 nearest neighbour PSM method using the following variables from Census 2011 for matching: distance between village and block headquarters (kilometres); population; % of schedule caste or schedule tribe households; if a village is served by public transport; if a village is connected to a major road; if a village has a public ration shop; if a village has a post office; if a village has a bank; % of households in a village with a bank account; if a village has an agricultural society; if a villages has a self-help group; % of households in a village serviced by closed drainage system; % of households in a village with improved source of drinking water; % of households in a village with improved sanitation facility; % of households in a village using electricity as the main source of light; % of households in a village with a *pucca* house; household asset index for the village).^20–23^

Table 1 summarises the matching performance in terms of reduction in the sum of standardised mean bias after matching. The standardised mean bias was reduced by 61%–81% after matching across the six district pairs. The Log Reduction test statistic before matching was statistically significant (p<0.001), but became insignificant after matching (p>0.75), suggesting that both groups are statistically similar on average after the matching procedure. We then selected the best matched village pairs– in terms of the difference in the propensity scores of the matched pairs –35 pairs of villages for each intervention block in MP and 24 pairs of villages for each intervention block in Bihar. Overall, we selected 216 matched pairs (432 villages) in Bihar and 210 matched pairs (420 villages) in MP.

**Table 1 T1:** Comparison of matching performance in reducing bias

	Madhya Pradesh			Bihar		
	Ujjain-Dewas	Barwani-Alirajpur	Katni-Jabalpur	Samastipur-Darbhanga	Lakhisarai- Muzaffarpur	Sitamarhi-Jamui
Standardised mean bias - before matching	16.6	27.5	40.3	27	35.4	40.8
Standardised mean bias - after matching	6.5	8	9.9	8.3	6.6	9.7
% reduction in mean bias	61%	71%	75%	69%	81%	76%
P-value of LR test - before matching	0.000	0.000	0.000	0.000	0.000	0.000
P-value of LR test - after matching	0.929	0.929	0.905	0.788	0.997	0.490
Mean difference in propensity score	0.002	0.072	0.131	0.004	0.046	0.181

LR, log reduction.

*Recruitment of Study Participants*: In the already conducted baseline survey, we randomly sampled one AWC if more than one AWC existed in a selected village. Using the list of beneficiaries available at the selected AWC as a sample frame, we randomly sampled four mother-child dyads after stratification by life-stages: (1) mother of child aged <3 months, (2) mother of child aged three to <6 months, (3) mother of child aged six to <12 months and (4) mother of child aged 12 to <24 months. Additionally, we randomly sampled up to five pregnant women or mothers with a child <3 months for more in-depth analysis of ICDS services during pregnancy and child birth. To measure AWC-level outcomes, we conduct a survey of the selected AWWs as well.

The endline will be a repeated cross-sectional sample where pregnant women and mothers with children <12 months will be recruited using the list of beneficiaries available at the AWC at that time. We do not plan to recruit children older than 12 months at the endline because the ICDS-CAS intervention would be active for <12 months and we can realistically measure the changes only among children who were born after the ICDS-CAS implementation started.

All survey participants are/will be recruited for the study after being administered informed consent as per the Institutional Review Board approved protocol. Additional assent is taken just before taking anthropometric measurements (height and weight) of the children.

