With a goal to improve the functioning of ICDS, the Government of India launched the ICDS Systems Strengthening and Nutrition Improvement Programme (ISSNIP) in 2012 which focused on infrastructure upgradation and training of AWWs to build their knowledge on health and nutrition topics under the Incremental Learning Approach. At the same time, a pilot-scale mHealth intervention to improve ICDS service delivery was implemented in Bihar between 2012 and 2013. A randomised controlled trial of this intervention found a significant increase in the proportion of beneficiaries receiving visits from frontline workers at different life-stages - last trimester of pregnancy (42% vs 52%), first week after delivery (60% vs 73%) and complementary feeding stage >5 months after delivery (36% vs 45%).^12^ The intervention also significantly increased the proportion of beneficiaries receiving at least three antenatal care visits (29% vs 50%), the proportion of beneficiaries consuming at least 90 iron folic acid tablets during pregnancy (11% vs 17%), the proportion of mothers breastfeeding immediately after birth (62% vs 76%) and the proportion of mothers starting complementary feeding at the right time (32% vs 41%). Subsequently, the ISSNIP was restructured in 2015 by integrating ICDS in seven states with an at-scale mHealth intervention called Common Application Software (ICDS-CAS) installed on smart phones and with accompanying multilevel data dashboards. This system is intended to be a job aid for frontline workers, supervisors and managers, and aims to ensure better service delivery and supervision by enabling real-time monitoring and data-based decision-making.

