### Sample design and power calculations

The initial sample size was determined as 400 villages in each arm with one AWW and, on average, three mother-child dyads in each village to measure a relative effect of 15% in a standardised counterfactual outcome [Normal(0,1)], with a significance level of 0.05, power of 80% and intra-cluster correlation (ICC) of 0.15. The actual baseline survey sample consisted of 852 villages to account for refusals and loss to follow-up.

After the baseline survey was conducted in June-August 2017, completely separate from our efforts to design the evaluation, the Indian government decided to include ICDS-CAS in the National Nutrition Mission. Consequently, the original evaluation objectives were revised to estimate the effects of ICDS-CAS separately for MP and Bihar to draw deeper insights into the heterogeneity of impacts. Therefore, the evaluation sample needed to be powered to detect smaller magnitudes of effects on a few process-related secondary outcomes. We plan to increase the sample power by following the same panel of villages but recruiting almost twice as many participants in each village – up to two AWWs and up to eight mother-child dyads. Assuming 200 pairs of villages and 1200 mothers per arm in each state, the sample will have 80% power at a significance level of 0.05 to detect an absolute difference of 5%–9%-points from the counterfactual levels between 10%–50% with ICC between 0.15–0.30. With 400 AWWs per arm in each state, the sample will have 80% power to detect effects of 8–12%-points for AWW level outcomes from the counterfactual levels of 10%–40% with ICC between 0.25–0.45.

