### Analysis plan

The effects of the ICDS-CAS intervention will be estimated as,

$$Y_{ij,\;t=1}=\;\beta_{0}+\;\beta_{1}\;.\;T_{j}+Pair\;ID_{K}+{\overset{-}{Y}}_{j,t=0}\;+\;\varepsilon ,$$

where

$Y_{ij,\;t=1}$ = an outcome of interest for beneficiary *i* in village *j* at endline (*t*=1);

$T_{j}$ = indicator variable which is 1 for intervention and 0 for comparison villages;

$Pair\;ID_{K}$ = fixed effects to account for *k* pairs of matched villages;

${\overset{-}{Y}}_{j,t=0}$ = average pre-intervention or baseline (t = 0) level of the outcome Y in the village;

*ε* = the error term of the model; and

*β*
_1_ = the effect of the intervention on outcome Y.

We will adjust for the pre-intervention average level of outcome in a village (${\overset{-}{Y}}_{j,t=0}$) to control for, *at least*, the measured or unmeasured *time invariant* village-level and higher-level confounders. To the extent that the endline questionnaires or sampling are different from those in the baseline, the construction of the outcome indicators in the baseline and endline may differ slightly, but such differences (if any) will not affect the interpretation of impact parameters estimated using the above model specification. Additionally, as a consistency check, we will estimate adjusted treatment effects that control for any observed imbalance in important baseline covariates. We may additionally control for covariates that can help increase the precision of impact estimates. We do not plan to correct the p-values for multiple comparisons because we only test a limited number of indicators for primary outcomes. However, for secondary outcomes, when multiple indicators related to a topic or theme are compared, we will adjust the p-values for multiple comparisons. We also plan to estimate the effects by adjusting for pairing only at the district level and not at the village-level if accounting for village matching results in substantial sample loss. All analyses will be done in STATA and replicated by two different analysts.

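### The endline model has no life-stage term, so it is unbiased only if the life-stage mix of endline respondents is alike in both arms, which the article does not secure

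*Protocol article*

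**What the plan says.** - **Baseline sampling** (Recruitment of Study Participants). The paragraph opens with "In the already conducted baseline survey, we randomly sampled one AWC if more than one AWC existed in a selected village", and within the chosen AWC "we randomly sampled four mother-child dyads after stratification by life-stages". The four strata are child under 3, 3 to under 6, 6 to under 12, and 12 to under 24 months. In addition, "we randomly sampled up to five pregnant women or mothers with a child <3 months".
- **Endline sampling** (same section). A new cross-section in which "pregnant women and mothers with children <12 months will be recruited using the list of beneficiaries available at the AWC at that time". No life-stage strata or quotas are stated. Sample design and power calculations sets the number per village at "up to two AWWs and up to eight mother-child dyads".
- **Outcomes** (Primary outcomes). Adequate visits and appropriate counselling are both judged against what the guidelines require for the respondent's present life-stage or age. The supporting indicators are plain counts of visits and of messages recalled.
- **Model** (Analysis plan). The endline outcome is regressed on arm, matched-pair fixed effects and the village mean of the outcome at baseline. A consistency check adjusts for imbalance seen in baseline covariates. Beyond that, "We may additionally control for covariates that can help increase the precision of impact estimates". Life-stage is not named. The section adds that any difference between rounds in questionnaire or sampling leaves the reading of the effect estimates unchanged.
- **Intervention** (The ICDS-CAS intervention). The app replaces ten of eleven paper registers and tracks beneficiaries by name.

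**The concern.** The endline sampling frame is the AWC's own beneficiary list. In intervention villages the app changes how that list is kept; in comparison villages it does not. If pregnancies or births are registered earlier or more completely in one arm, the respondents there will have a different mix of life-stages.

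If outcome rates differ by stage, such a mix difference shows up in the treatment coefficient although no woman has received better service. The pair effects and the baseline mean are village-level quantities fixed before the endline respondents are drawn, so they cannot absorb it. The stage-specific thresholds may even out part of the variation for the two binary outcomes, but they do nothing for the supporting counts.

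**Working it through.** **1. The plan's own figure.** Inputs from Sample design and power calculations: 200 pairs and 1200 mothers per arm in each state, so 1200/200 = 6 per village; alpha 0.05 (taken as two-sided); power 80%; counterfactual rates 10% to 50%; ICC 0.15 to 0.30. The design effect is 1 + (6 − 1) × ICC, which is 1.75 or 2.50, and the effective number per arm is 1200 divided by it. Solving for the difference that gives 80% power:

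| Counterfactual | ICC 0.15 | ICC 0.30 |
|---|---|---|
| 10% | 5.0 points | 6.1 points |
| 40% | 7.5 points | 9.0 points |
| 50% | 7.5 points | 9.0 points |

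The stated 5 to 9 points is reproduced. The 5-point end belongs to a 10% rate. For the base rates used below, the relevant range is about 7.5 to 9 points.

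**2. Bias formula.** With no true effect, bias = sum over stages of (share in intervention arm − share in comparison arm) × outcome rate in that stage. For a shift between two stages this is shift × gap in rates.

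**3. Illustrative inputs.** The documents give no endline mix and no stage-specific rates for the primary outcomes. Background and problem context reports pilot visit coverage of 42% (last trimester), 60% (first week) and 36% (complementary feeding stage), reading the first of each pair as control. The widest gap is 60 − 36 = 24 points. The size of the shift is an assumption.

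- 5-point shift: 0.05 × 24 = 1.2 points.
- 10-point shift: 0.10 × 24 = 2.4 points.
- Wider range: 0.02 × 10 = 0.2 points up to 0.20 × 30 = 6.0 points.

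**4. Effect on false positives.** At a 50% rate and ICC 0.15, SE = √(2 × 0.5 × 0.5 × 1.75 / 1200) = 2.70 points. A bias of 1.2 or 2.4 points raises the two-sided type I error from 5% to about 7% or 14%. At ICC 0.30 (SE 3.23 points) the figures are about 7% and 12%.

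**5. Chance imbalance is not the issue.** For a stage holding 25% of respondents, the SD of the difference in share is √(2 × 0.25 × 0.75 / 1200) = 1.8 points. At a 24-point gap that is 0.018 × 24 = about 0.4 points, and it is already part of the sampling error. Only a systematic difference matters.

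**6. Simulation of the written model.** 200 pairs, 6 mothers per village, three stages at the pilot rates, no true effect, 400 runs. Results in percentage points:

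| Shift in mix | Mean estimate (SD), model as written | Mean estimate (SD), with stage indicators |
|---|---|---|
| None | −0.06 (2.08) | −0.03 (2.05) |
| 5 points | 1.13 (2.21) | −0.05 (2.13) |
| 10 points | 2.38 (2.12) | 0.02 (2.06) |

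Pair effects and the baseline mean leave the bias almost whole. Stage indicators remove it, and the spread is no larger.

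**The case against.** **Stratification as the cause.** A reader might infer that stratified sampling itself creates the bias. The documents do not support this. The strata describe the baseline survey, not the analysed sample, and the same rule applied in both arms tends to balance the mix. With equal mix the simulated bias is nil, with or without the term.

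**A contaminated baseline mean.** A reader might also infer that the baseline village mean includes mothers of children aged 12 to under 24 months. The primary outcomes are defined only for pregnant women and mothers of children under 12 months, so that stratum may already be excluded. What remains is that the additional draw at baseline, of up to five women who are pregnant or have a child under 3 months, can vary in number by village.

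**The figures are borrowed.** This stands. The pilot rates are receipt of visits in particular windows, not an adequate number in the past 3 months, and the first week is not the whole stage under 3 months. Stage-specific thresholds may narrow the gap. The shifts have no source in the documents and are placed between the two most distant stages.

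**Detail for the analysis plan.** Endline quotas and a covariate list may stand in a fuller document, and the article does not say that life-stage will be left out. That is fair, and it limits the point to an improvement. But the article writes out the model and makes a definite claim that sampling differences are harmless. Its two provisions for covariates do not cover the case: one is tied to baseline imbalance, the other is optional and names nothing.

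**Conclusion.** The point holds as a conditional weakness in a written model. Both primary outcomes depend on life-stage, the endline frame is a list that the intervention may alter in one arm, and nothing in the equation removes a resulting difference in stage mix. The claim that sampling differences do not affect interpretation is true only when the endline mix is alike in both arms.

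It would be too strong to say that the effect estimate is biased. No difference in mix is shown, and the bias is zero if the mix is equal or if outcome rates do not vary by stage. Under the assumptions shown, the size is 1.2 to 2.4 points against a detectable difference of about 7.5 to 9 points: enough to distort a borderline result, not enough to create a large one. The change is worth making because it guards against this at no loss of precision.

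**What to change.** 1. Add life-stage indicators (pregnant; child under 3, 3 to under 6, 6 to under 12 months) to the Analysis plan model for every beneficiary-level outcome.
2. State whether endline recruitment uses life-stage quotas and, if so, that they are the same in both arms. Report the stage mix by arm in either case.
3. Compute the baseline village mean on the same life-stages as the endline outcome.
4. Qualify the statement on sampling differences: it holds if the endline stage mix is alike in both arms or is adjusted for.

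The cost is wording and a few lines of code. Life-stage must be recorded anyway to score each respondent, and three extra coefficients are negligible with 1200 mothers per arm in each state. One limit should be stated: if the app also changes which women within a stage are listed, stage adjustment does not remove that selection.

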Figure 1 presents the ICDS-CAS information flow from the AWC through to the MWCD. The logic model in figure 2 summarises how ICDS-CAS is expected to improve service delivery, and ultimately improve health and nutritional outcomes in mothers and their children. The listed short-term outcomes are those expected to be achieved in the planned evaluation follow-up period of <12 months. The longer-term outcomes related to improved health and nutrition will be measured (except improvements in cognitive abilities) and analysed from a learning perspective, but these remain aspirational in the context of this evaluation study.

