### Primary outcomes

The primary outcomes to assess the effectiveness of ICDS-CAS compared with the standard ISSNIP and ICDS are:The proportion of pregnant women and mothers of children <12 months who received adequate number of home visits by AWWs in the past 3 months (adequate number will be the minimum number of visits a respondent must receive as per ICDS guidelines for the current life-stage/age. Additionally, we will use, as a supporting indicator, the number of visits as a continuous outcome indicator.^26^); andThe proportion of pregnant women and mothers of children <12 months who received appropriate extent or level of counselling from AWWs during their interactions (at home, at AWCs or in other settings) in the past 3 months (appropriate level of counselling will be a recall of at least half of the correct messages/counselling that a respondent should receive as per ICDS guidelines for the current life-stage/age. Additionally, we will use, as a supporting indicator, number of correct messages or services recalled by the respondent as a continuous outcome.^26^).

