### Outcome measurements

All beneficiary-level and AWW-level outcomes will be measured through structured interviews, with verification of registers and documents wherever possible. The household instruments were developed using standard questions from the WHO and Demographic and Health Survey frameworks, and capture information about the demographic and socio-economic characteristics of the household, birth history and family planning, pregnancy care, awareness and utilisation of AWC services at different life-stages, IYCF practices, immunisation, knowledge of health and nutrition and child health and nutritional outcomes (child growth). The AWW instrument captures information about coverage of beneficiaries, service delivery, supervisory support, work incentives and motivation, training received, time allocation, knowledge, and infrastructure and supplies at the AWC. The interviews are administered in *Hindi* on an android tablet-based SurveyCTO^TM^ platform.

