## Discussion

The evaluation will provide evidence on whether and to what extent ICDS-CAS mHealth can improve health and nutrition service delivery beyond what is feasible with traditional non-technology-based approaches under ISSNIP. Additionally, the analysis of a range of lower order outputs and outcomes can help us identify the pathways through which ICDS-CAS has worked, or the critical failure points.

The study faces a few limitations in identifying unbiased estimates of the programme effects due to the nature of the intervention and constraints on the study design. First, confounding or selection bias cannot be theoretically ruled out in an observational study such as ours. While the matching procedure appears to be successful, it may not have removed all residual and unobserved confounding. Measurement biases including the Hawthorne effect^27^ are possible because the outcomes are measured through interview recalls and observations. The external validity of the findings can be questioned because the purposive sampling of states, pairing of districts and the PSM-based sampling of villages do not result in a statistically representative sample of entire ICDS-CAS programme area. Finally, as is the case with most large-scale programmes, ICDS-CAS implementation may be delayed and the planned follow-up period may not be adequate for the impacts to materialise.

While these limitations are common in observational studies, the study team has tried to minimise the risk to validity of the findings by reducing the observed pre-intervention imbalance using a large set of variables from Census 2011 for matching, controlling for at least the cluster level time-invariant confounders by using a repeated cross sectional design, measuring the primary outcomes at the beneficiary level (beneficiaries will be blinded to their intervention status in the study), measuring a large set of indicators as per the logic model to test whether ICDS-CAS is working through hypothesised pathways and delaying the endline survey as much as possible before the intervention is implemented in the control districts. The evaluation framework also includes other components which can assess the intervention using mixed-methods approaches, and can help build confidence in the study findings.

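### The <12-month endline age limit does not confine the sample to post-launch births, so secondary outcomes fixed at delivery or in pregnancy may be diluted

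*Protocol article*

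**What the plan says.** Under Sampling and recruitment of study participants (Recruitment of Study Participants), the endline rule is that "pregnant women and mothers with children <12 months will be recruited using the list of beneficiaries available at the AWC at that time". Older children are left out on the stated ground that "we can realistically measure the changes only among children who were born after the ICDS-CAS implementation started". That sentence also gives the expected exposure at endline, namely that "the ICDS-CAS intervention would be active for <12 months". No birth-date condition tied to launch is given.

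The section on the ICDS-CAS intervention repeats a "planned evaluation follow-up period of <12 months", and the Discussion allows that "ICDS-CAS implementation may be delayed and the planned follow-up period may not be adequate for the impacts to materialise". The launch date and the exact length of exposure are not stated.

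The first primary outcome is the proportion who "received adequate number of home visits by AWWs in the past 3 months"; the counselling outcome has the same 3-month window. Outcome measurements says the household instrument also covers "birth history and family planning, pregnancy care, awareness and utilisation of AWC services at different life-stages". Secondary outcomes lists IFA provision among the additional services, and knowledge and practices at beneficiary level. In the Analysis plan, exposure is a village indicator, T_j, with no term for date of birth or launch.

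**The concern.** An age limit of 12 months is the same as birth after launch only when the programme has run for at least 12 months, and the plan says it will not have. By the plan's own criterion, then, the endline sample includes infants in whom change cannot be measured, at least for events around birth and before it.

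What is at stake is a set of secondary outcomes. If antenatal care, IFA in the last pregnancy, or practice at delivery is asked of every mother of an infant, some answers describe events that pre-date the programme. In intervention villages those answers are coded as treated, which shrinks the estimated effect. The Discussion intends to use lower-order results to find the pathways that worked and the points of failure. A small effect caused by pre-launch events could be mistaken for such a failure.

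**Working it through.** **Inputs.** From the article: endline age below 12 months; programme active for M<12 months; 3-month recall for the primary outcomes; and, per state, 200 pairs and 1200 mothers per arm (6 per village), 80% power, alpha 0.05, ICC 0.15–0.30, counterfactual 10%–50%. Assumptions: M itself; a two-sided test; ages either even over 0–12 months or in equal thirds across <3, 3–<6 and 6–<12 months (the baseline life-stages; the endline mix is not given); a third trimester of 3 months; complementary feeding starting at about 6 months of age.

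**1. The plan's own figure.** Effective n per arm = 1200/(1 + 5 × ICC).
- ICC 0.15: 1200/1.75 = 686. From 10%, the detectable difference is 5.0 points.
- ICC 0.30: 1200/2.5 = 480. From 50%, it is 9.0 points.

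This reproduces the stated 5–9 points.

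**2. Share of infants born before launch.** Even ages: (12 − M)/12. Equal strata, for M between 6 and 12: one third × (12 − M)/6.

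**3. Share whose third trimester lies wholly after launch.** The child must be younger than M − 3 months, so with even ages the share is (M − 3)/12.

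| M (months) | Born before launch, even ages | Born before launch, equal strata | Third trimester wholly after launch, even ages |
|---|---|---|---|
| 6 | 50% | 33% | 25% |
| 9 | 25% | 17% | 50% |
| 11 | 8% | 6% | 67% |

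The pre-launch share is above zero for every M below 12.

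**4. Effect on an outcome fixed at birth.** Assume even ages, all infants in the denominator, no effect on pre-launch births and the full effect on later ones. Then observed effect = true effect × M/12. The restricted analysis keeps 1200 × M/12 mothers per arm and 6 × M/12 per village, with the full effect. For example, at M = 9 and ICC 0.15 the effective n is 900/(1 + 3.5 × 0.15) = 590.

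| M | 5 points becomes | Power, all infants | Power, restricted | 9 points becomes | Power, all infants | Power, restricted |
|---|---|---|---|---|---|---|
| 6 | 2.5 | 31% | 63% | 4.5 | 29% | 70% |
| 9 | 3.75 | 57% | 74% | 6.75 | 55% | 76% |
| 11 | 4.6 | 73% | 78% | 8.25 | 73% | 79% |

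The 5-point columns use 10% and ICC 0.15; the 9-point columns use 50% and ICC 0.30. Against the 80% reference, restriction loses less power than dilution does.

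**5. Outcomes not affected.** The 3-month window of the primary outcomes lies wholly after launch once M ≥ 3. If complementary feeding starts at about 6 months of age, a child under 12 months reached that point at most 6 months before endline, so it is post-launch once M ≥ 6.

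**The case against.** The strongest reply is that the sentence explains only why children over 12 months are excluded. That exclusion is valid: with less than 12 months of activity, all of them pre-date launch. The text does not say outright that every recruited infant was born after launch. This is fair, but the criterion given for the exclusion applies equally to infants aged M to 12 months, and those are kept.

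Second, the affected outcomes are partly inferred. Pregnancy care and birth history appear as questionnaire content, not as defined outcomes, and the article does not say who supplies each secondary outcome. Currently pregnant women are also recruited. At baseline, an extra sample of pregnant women or mothers of children under 3 months was drawn to study services around pregnancy and birth. If the endline used only that group, every birth would be post-launch once M ≥ 3. An analysis plan may say so. This makes the dilution conditional; it does not repair the rationale.

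Third, the article already warns that follow-up may be too short and that higher-order effects may be underestimated. That caution helps, but it concerns time for the programme to take hold, not the counting of events that preceded it.

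A reader might infer more than the text supports:
- That the primary results are diluted. The 3-month recall rules this out for M ≥ 3.
- That pregnancy outcomes are almost wholly unexposed because few complete pregnancies follow launch. That demands exposure for all nine months; the third-trimester shares above are much higher.
- That delay is expected. The Discussion says only that it may occur.

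**Conclusion.** The point holds in a limited form. The age limit does not meet the criterion offered for it, and neither the recruitment rule nor the village-level model removes pre-launch births. The consequence is confined to secondary outcomes fixed at delivery or during pregnancy, and arises only if they are taken from all mothers of infants. Its size cannot be pinned down, because M, the endline age mix and the outcome denominators are not stated. It ranges from slight when M is near 12 to a halving of a birth-time effect at M = 6 with even ages. It is worth correcting before the endline analysis, but does not threaten the main conclusions.

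**What to change.** 1. Reword the rationale: the limit excludes children who must have been born before launch, but does not ensure that those recruited were born after it.
2. Obtain the launch date for each intervention block from the implementing agencies and assign it to the paired comparison villages. The article does not show that these dates are already held.
3. For each delivery- or pregnancy-related secondary outcome, define the event window (for example delivery, or the third trimester). Make the main analysis, in both arms, the respondents whose window falls after the assigned date. Show the all-infants estimate beside it.
4. Leave recruitment and the two primary outcomes unchanged, and confirm that the 3-month recall falls wholly after launch.

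The cost is a date request, a filter applied equally in both arms, and fewer respondents with less precision for those secondary outcomes. Some villages may have no eligible respondent left, so pairs could be lost; the plan's existing fallback of adjusting for district pairing would then apply.
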